### Adverse events management

Bradycardia: Defined as heart rate <40 bpm or 30% below baseline. Administer intravenous atropine 0.5 mg, repeatable at 5–10 min intervals as clinically indicated.Tachycardia: Defined as heart rate >100 bpm or 30% above baseline. For hypovolemic patients, administer crystalloid solutions; for euvolemic patients, consider esmolol infusion.Hypotension: Systolic blood pressure <80 mmHg or >30% decrease from baseline. Following volume status assessment, implement volume expansion, vasopressor administration, and/or inotropic support.Hypertension: Systolic blood pressure >180 mmHg or >30% increase from baseline. Administer intravenous urapidil.Hypoxia: SpO2 < 90%. Implement supplemental oxygen, deep breathing/coughing, chest physiotherapy, non-invasive ventilation or mechanical ventilation as required.Device-related complications: Needle breakage, intractable pain, local hematoma, infection, or patient intolerance.

All adverse events require detailed documentation and clinical monitoring until resolution.

### Sample size estimation

Based on existing literature (8), PONV incidence in the control group is estimated to be 61% (p_1_ = 0.610). We anticipate that by minimizing risk strategies and acupoint stimulation, we hypothesize a 30% relative reduction in PONV incidence following bilateral orthognathic surgery [p_2_ = p_1_ × (1–0.3) = 0.610 × 0.7 = 0.427]. The 2020 Fourth Consensus Guidelines for PONV established equivalent efficacy between PC6 acupoint stimulation and pharmacological prophylaxis regarding nausea control, vomiting reduction, and rescue antiemetic requirements. Therefore, this trial aims to assess the combinatorial effect of acupuncture, dexamethasone, and palonosetron on PONV incidence reduction in patients undergoing bilateral orthognathic surgery, using a two independent-sample superiority test for sample size calculation. A one-sided superiority test is employed, with a significance level *α* set at 0.05, and Zα being 1.645. The statistical power (confidence level) is 1-*β*, which is 0.8, and Zβ is 0.84. The sample size per group is calculated using the formula:

$$n=\frac{{\left(Z_{\alpha }\sqrt{2\bar{p}(1-\bar{p})}+Z_{\beta }\sqrt{p_{1}(1-p_{1})+p_{2}(1-p_{2})}\right)}^{2}}{{\left(p_{1}-p_{2}\right)}^{2}}$$

The derived minimum sample size per group is 92 (total *N* = 184). Accounting for 10% attrition and implementing stratified randomization with block size 4, the adjusted final enrollment target reaches 104 participants per group (total *N* = 208).

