**Methods:**

This single-center, double-blind, randomized controlled trial will enroll 216 participants allocated to two groups: group A, the acupoint stimulation group and group B, the sham stimulation group. All subjects will receive standardized PONV prophylaxis including dexamethasone 5 mg IV, palonosetron 0.075 mg IV, target-controlled propofol infusion (0.5 μg/mL), and laryngeal packing following anesthesia induction. Patients in both groups receive two sterile thumb-tack needles – one real needle and one identical-appearing sham needle without a pointed tip. In group A, the real needles are placed at the PC6 acupoint, and the sham needles are placed at the sham acupoint on the forearm. In group B, the real needles are placed at the sham acupoint, while the sham needles are placed on the PC6 acupoint. Finally, all patients will have the sterile opaque patches applied to each acupoint for allocation concealment. The needles will remain in place up to 24 h postoperatively at least. The primary outcome will be the incidence of PONV at 24 h postoperatively. Secondary outcomes will include the incidence rates of PONV at different postoperative intervals and a 15-point quality of life recovery score at 24 h postoperatively.

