### Intervention

Upon entering the operating room, the acupuncturist generates a randomization sequence via the Random.org website (https://www.random.org/) to access the corresponding sealed envelope containing group allocation details. Before induction of anesthesia, the acupuncturist applies the assigned thumb-tack devices bilaterally according to the randomized allocation. Both groups receive two thumb-tack devices: a real needle (0.25 mm × 2.0 mm, disposable sterile press needles) and a sham needle with identical appearance but no needle tip. In Group A, the real device is bilaterally applied to the PC6 acupoint – located three finger breadths proximal to the wrist crease between the palmaris longus and flexor carpi radialis tendons – while the sham device is bilaterally positioned at the non-acupoint site six finger breadths proximal to the wrist crease and 2 cm ulnarly. Group B receives the inverse configuration, with sham stimulation bilaterally at PC6 and real stimulation bilaterally at the non-acupoint site. The sham site maintains a 3 cm radius free of established acupoints to prevent collateral stimulation (Figure 3). No deliberate De Qi sensation is elicited during application. Opaque sterile patches will be applied to both intervention sites to conceal the allocation information (Figure 4), with devices remaining *in situ* for 24 postoperative hours. All acupuncture-related procedures are performed in strict accordance with aseptic principles to minimize the risk of infection. Both groups receive standardized PONV prophylaxis per guidelines (18): dexamethasone 5 mg, palonosetron 0.075 mg, propofol target-controlled infusion (TCI) 0.5 μg/mL, and pharyngeal packing.

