### Statistical analysis

The statistical analysis will be performed with the SPSS 25.0 software. Continuous variables are reported as mean ± standard deviation (SD) or median (interquartile range), while categorical variables are expressed as frequencies or percentages. Parametric data were analyzed using ANOVA or the Kruskal-Wallis H-test, whereas nonparametric comparisons employed chi-square tests (*χ*^2^ tests) or Fisher’s exact probability tests. The primary outcome is the 24-h PONV incidence rate. Superiority testing will assess whether the experimental intervention’s efficacy exceeds that of the control group, derived from literature-derived baseline PONV incidence (control group p₁ = 0.610) and hypothesized 30% relative risk reduction (experimental group p₂ = 0.427). The predefined superiority margin (*δ*) is set as an 18.3% absolute risk reduction (i.e., the incidence in the experimental group must be ≤ the incidence in the control group – δ, where *δ* = 0.183). A single-tailed *Z*-test will be used to compare the incidence difference between the two groups, calculating the risk difference (risk difference, RD) with corresponding 97.5% one-sided confidence interval (equivalent to 95% two-sided CI upper bound). Superiority will be established if the CI upper limit for RD remains below *δ*. Relative risk (RR) with 95% CI will supplement these analyses. Nonparametric alternatives (Fisher’s exact test) will substitute when normal approximation assumptions are violated. Post-hoc exploratory analyses are used to examine heterogeneity in the primary outcome across predefined subgroups, including age <25 years, female sex, history of motion sickness/PONV, smoking status, surgery duration >200 min, and hypotension duration >60 min. Logistic regression is employed to adjust for treatment-covariate interactions of subgroup factors. A *p*-value <0.05 will be considered statistically significant. Except for the superiority test, which employs a one-sided test, all other tests are two-sided.

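### The 30% reduction behind the sample size is credited jointly to risk-minimising measures and acupuncture, but both arms receive those measures, so the 80% power is supported for real versus sham PC6 only under conditions the protocol does not state

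*Protocol article*

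**What the plan says.** Under Sample size estimation, the article sets the control rate: "PONV incidence in the control group is estimated to be 61"%, taken from one cited study. The effect follows: "We anticipate that by minimizing risk strategies and acupoint stimulation, we hypothesize a 30% relative reduction in PONV incidence following bilateral orthognathic surgery", with the treated rate computed as "0.610 × 0.7 = 0.427". The same paragraph then describes the trial's aim as assessing the combined effect of acupuncture, dexamethasone and palonosetron. "A one-sided superiority test is employed" at alpha 0.05 with power 0.8, giving 92 per group.

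The shared measures are described in two places. The Abstract states "All subjects will receive standardized PONV prophylaxis" and the Intervention section states "Both groups receive standardized PONV prophylaxis per guidelines". Both list dexamethasone, palonosetron, target-controlled propofol and a throat pack. The arms differ only in needle placement: real at PC6 and sham at the non-acupoint site, or the reverse. The last paragraph of the Background gives the question as the added benefit of acupoint stimulation over routine prevention.

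Under Statistical analysis the assumed difference is used again, as the superiority margin, which "is set as an 18.3% absolute risk reduction".

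**The concern.** A randomised comparison estimates only what differs between the arms. Any part of the 30% that comes from measures given to everyone lowers PONV in the control arm too and drops out of the difference. The sample size sentence credits the 30% to those measures and acupuncture together, and the stated aim in the same paragraph repeats the joint framing. The calculation nevertheless treats the whole 18.3 points as a between-arm difference. No section gives an effect for PC6 needling on top of the shared regimen.

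Two things are at stake. If the PC6-only effect is smaller than 18.3 points, a negative result could be read as showing that acupuncture adds nothing, although the trial had not been shown to have adequate power for that effect. The same 18.3 points also enter the success criterion.

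**Working it through.** **Inputs** (Sample size estimation): control rate c = 0.610, treated rate t = 0.427, one-sided alpha 0.05 (Z = 1.645), power 0.8 (Z = 0.84), 1:1 allocation.

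**Reproducing the plan's figure.** With p̄ = (0.610 + 0.427)/2 = 0.5185:

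- √(2 × 0.5185 × 0.4815) = 0.7066
- √(0.610 × 0.390 + 0.427 × 0.573) = 0.6947
- n = (1.645 × 0.7066 + 0.84 × 0.6947)² / 0.183² = 3.0482 / 0.033489 = 91.02, so 92 per group

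The arithmetic is sound. The question is what the 0.183 represents.

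**Power formula** (the printed formula solved for power):

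Power = Φ{ [(c − t)√n − 1.645 √(2p̄(1 − p̄))] / √(c(1 − c) + t(1 − t)) }

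At 0.610 versus 0.427 and n = 92 this gives 80.3%.

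The article does not split the 30% between shared measures and PC6, so both sets of scenarios below are assumptions.

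**Scenario 1: treated rate stays at 42.7% and a share s of the reduction also reaches the control arm.** Then c = 0.610 × (1 − 0.30 × s). For s = 1/3: c = 0.549, p̄ = 0.488, 0.122 × √92 = 1.1702, 1.645 × 0.7069 = 1.1629, and Φ(0.0073 / 0.7016) = Φ(0.0104) = 50.4%.

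| Share s | Control rate | Difference (points) | Power, 92 per group | Power, 97 per group |
|---|---|---|---|---|
| 0 | 61.0% | 18.3 | 80.3% | 82.2% |
| 1/10 | 59.2% | 16.5 | 72.5% | 74.5% |
| 1/5 | 57.3% | 14.6 | 63.5% | 65.5% |
| 1/3 | 54.9% | 12.2 | 50.4% | 52.2% |
| 1/2 | 51.9% | 9.2 | 34.3% | 35.6% |

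The 97 column takes the enrolment of 216 given in the Abstract and the recruitment and randomisation sections, less 10% attrition (108 × 0.9 = 97.2).

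**Scenario 2: shared measures lower the control rate, but PC6 keeps a 30% relative reduction.** Then t = 0.7c.

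| Control rate | Treated rate | Difference (points) | Power, 92 per group |
|---|---|---|---|
| 58% | 40.6% | 17.4 | 76.6% |
| 55% | 38.5% | 16.5 | 72.8% |
| 50% | 35.0% | 15.0 | 66.2% |

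Scenario 1 is the harsher model, because every shared point comes off the PC6 effect. Scenario 2 is milder, because only the baseline moves.

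**The margin.** The parenthesis under Statistical analysis requires the experimental incidence to lie at least 18.3 points below control. If the 97.5% one-sided limit must clear that margin and the true difference is exactly 18.3 points, the truth sits on the boundary of the hypothesis being tested. The rule then succeeds with probability P(Z > 1.96), about 2.5%.

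**The case against.** The strongest reply is that 61% already is the rate under prophylaxis. The sample size section labels it the control-group incidence, and the control group receives every shared measure. The Background says PONV reaches about 60% in orthognathic patients even though dexamethasone and 5-HT3 antagonists are routinely given. The sentence crediting both components is loosely written and could describe group A's whole regimen set against a control arm already on prophylaxis. The Statistical analysis section pairs 0.610 with control and 0.427 with experimental without mentioning a bundle. The sample size section also cites guideline support for PC6, which suggests that an acupuncture effect was in mind. On that reading, 80% power holds for the randomised contrast.

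Much of this stands. A reader might infer from the joint wording that the trial is underpowered, or that 80% power cannot apply to real versus sham PC6. The document does not support either inference. If 61% is the rate under the full shared regimen and PC6 alone gives 18.3 points, the calculation is right, however much the shared measures contribute.

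The reply does not settle the matter. Nothing shows that the 61% includes target-controlled propofol and pharyngeal packing. If the risk strategies are already in the 61%, they cannot be credited again for the 30%; if they are further measures, they lower both arms. The guideline support concerns equivalence of PC6 stimulation and drug prophylaxis, which is not an effect added to two drugs. The Background itself notes that earlier trials mostly tested acupuncture alone against single agents. The Limitations section openly discloses that needling at the sham site may narrow the difference, but the calculation makes no allowance for it.

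**Conclusion.** The point holds in conditional form. The arithmetic is correct, but the effect size is justified by a combination that the randomised contrast does not test. The 80% is supported for real versus sham PC6 only under two unstated conditions: a 61% control rate under all shared measures, and the whole 18.3 points from PC6 needling alone.

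The size of any loss is unknown. At 92 per group and one-sided 0.05, the assumed scenarios run from 76.6% (PC6 keeps its 30% relative reduction, control rate 58%) to 34.3% (half the reduction shared, treated rate held at 42.7%). They show how sensitive the power is to the unstated inputs and are not estimates of the trial's actual power. Enrolling 216 changes them little.

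Using the assumed effect as the margin is a fault whichever reading is correct. The mismatch between alpha 0.05 and the 97.5% one-sided interval, and the totals of 208 and 216, are separate issues and play no part in this conclusion.

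**What to change.** Under Sample size estimation, state the PONV rate expected in a control arm receiving every shared measure, and the reduction attributed to PC6 needling alone, with the reason for each. If 30% was meant for PC6 alone, saying so and justifying it answers the attribution point. Keep the enrolment and restate the power over a range of PC6-only differences. From a 61% control rate, with 92 per group and one-sided 0.05, the formula above gives:

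| PC6-only difference (points) | Power |
|---|---|
| 18 | 79.2% |
| 15 | 65.5% |
| 12 | 49.6% |
| 9 | 33.9% |

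A second column at the control rate judged realistic under the full regimen would complete the table if that rate is not 61%.

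Under Statistical analysis, remove the 18.3 points from the decision rule and test superiority against a difference of zero.

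The cost is a few sentences and a short table. No extra patients are needed and the intervention does not change. The stated power may look less favourable.

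### The sample size is set at one-sided alpha 0.05, but superiority is judged with a 97.5% one-sided limit; against a zero-difference null the stated 80% power is then about 70% to 77%

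*Protocol article*

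**What the plan says.** Sample size estimation: "A one-sided superiority test is employed, with a significance level" α "set at 0.05, and Zα being 1.645". The power is 1-β, "which is 0.8, and Zβ is 0.84". The control rate is 0.610 and the experimental rate follows from a 30% relative reduction ("0.610 × 0.7 = 0.427"). The result is given as "The derived minimum sample size per group is 92", 184 in total. "Accounting for 10% attrition and implementing stratified randomization with block size 4", the section arrives at 104 per group (208). The Abstract, the recruitment section and the randomisation section give 216 instead, which is 108 per group.

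Statistical analysis: the primary comparison is a single-tailed Z-test on the difference in incidence, accompanied by a risk difference (RD) with a "97.5% one-sided confidence interval (equivalent to 95% two-sided CI upper bound"). Superiority is declared when the upper limit for RD lies below δ, and δ is set at 0.183. The section ends with a general p < 0.05 threshold and confirms that the superiority test is one-sided.

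**The concern.** A one-sided test at 0.05 uses the critical value 1.645. A 97.5% one-sided limit uses 1.96. The plan applies the first to sizing and, through its p < 0.05 threshold, to the Z-test. It applies the second to the interval that establishes superiority. The gloss equating the limit with the upper bound of a two-sided 95% interval indicates that 97.5% is deliberate and not a misprint.

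Two things are at stake. The 80% power was calculated for a more lenient criterion than the interval applies. And one primary claim has two nominal error rates attached to it, which can give different answers on the same data.

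**Working it through.** **Inputs** (Sample size estimation): p1 = 0.610, p2 = 0.427, difference 0.183, mean p̄ = (0.610 + 0.427)/2 = 0.5185, Zα = 1.645, Zβ = 0.84.

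**Formula printed in the protocol** (its null is a difference of zero):

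n = [Zα·√(2p̄(1−p̄)) + Zβ·√(p1(1−p1) + p2(1−p2))]² / (p1−p2)²

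- √(2 × 0.5185 × 0.4815) = 0.7066
- √(0.2379 + 0.2447) = 0.6947
- (p1−p2)² = 0.183² = 0.03349

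**Step 1, the plan's own figure.** With Zα = 1.645: (1.1624 + 0.5835)² / 0.03349 = 91.02, so 92 per group. The stated figure is reproduced.

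**Step 2, the level of the confidence limit.** With Zα = 1.96: (1.3850 + 0.5835)² / 0.03349 = 115.7, so 116 per group.

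**Step 3, power at each level.** Power = Φ[(0.183·√n − Zα × 0.7066)/0.6947]. For n = 92 and Zα = 1.96: (1.7553 − 1.3850)/0.6947 = 0.533, and Φ(0.533) = 0.703.

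| Evaluable per group | Where it comes from | Power, one-sided 0.05 | Power, one-sided 0.025 |
|---|---|---|---|
| 92 | stated minimum | 80.3% | 70.3% |
| 93 to 94 | 104 × 0.9 = 93.6 | 80.7% to 81.1% | 70.8% to 71.2% |
| 97 | 108 × 0.9 = 97.2 | 82.2% | 72.6% |
| 104 | 208 enrolled, no loss | 84.5% | 75.6% |
| 108 | 216 enrolled, no loss | 85.7% | 77.2% |

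At 92 per group and one-sided 0.025, a Wald-interval approximation gives 71.5% and exact binomial enumeration of the Wald limit gives 69.6%, so the choice of method matters little.

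**Step 4, can the two criteria disagree?** Take 92 per group, with 56 events in control and 43 in the experimental group. RD (experimental minus control) = (43 − 56)/92 = −0.141; Z = 1.92; one-sided p = 0.027, significant at 0.05. The 97.5% upper limit is +0.001, which does not exclude zero. With 56 and 44 events, p = 0.038 and the upper limit is +0.012. Under the planned rates, exact enumeration at 92 per group gives a probability of about 9.4% that the test succeeds and the limit fails. The upper edge of the disagreement band sits slightly under 1.96 if the limit uses an unpooled standard error.

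**Step 5, the boundary.** Steps 2 to 4 compare the limit with 0. The plan's text compares it with δ. At 92 per group, with RD as experimental minus control:

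- Limit below +0.183: met about 99.9% of the time under the planned rates, and about 72% of the time when both arms have a rate of 0.61.
- Limit below −0.183, as the parenthesis defining δ implies: met about 2.5% to 2.8% of the time (by method) under the planned rates, and almost never under no difference.

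**The case against.** The strongest reply is that the written rule does not compare the limit with zero. A reader might infer that the trial's power simply is 70%, that its type I error is either 2.5% or 5%, and that any Z between 1.645 and 1.96 splits the test from the interval. The document does not support these as unconditional statements. Under the literal comparison with +0.183, the 56 versus 43 example passes both criteria, and the success rates are those in step 5. This objection stands. It limits the power and disagreement figures to a zero boundary, and it means that aligning alpha alone would leave a power statement that still does not describe the rule. It does not remove the mismatch, because the confidence level contradicts the sizing alpha whatever boundary is used.

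A reader might also infer that the governing criterion is open to free choice once the data are seen. That is too strong: only one sentence says how superiority is established, and it names the confidence limit. Some ambiguity does remain, because the sizing section fixes alpha at 0.05, the Z-test is named for the same comparison, and the p < 0.05 threshold has no exception for it.

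Third, 70% is the low end, since it assumes exactly 92 evaluable per group. That is fair, and the range is given above. Enrolling 216 does not close the gap, however: power is 77.2% with no loss and 72.6% after the protocol's own 10%. Losses do reduce the evaluable number, because the eligibility section excludes withdrawn cases from efficacy analysis.

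Lastly, a separate statistical analysis plan might settle the level. The protocol already states both levels, so this is a contradiction in its text and not a detail left for later.

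**Conclusion.** The inconsistency is real and should be corrected before the primary analysis. The arithmetic behind 92 per group is right for one-sided 0.05; the error is that the interval used to establish superiority runs at one-sided 0.025, with no reconciling sentence. At that level, 80% power needs 116 evaluable per group. The stated enrolments give about 70% to 77%, a shortfall of roughly 3 to 10 percentage points. The most relevant figure for 216 enrolled with 10% loss is about 73%.

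These sizes rest on the planned rates of 0.610 and 0.427, the normal-approximation formula in the protocol, and a boundary of zero for the risk difference. They are not the operating characteristics of the rule as literally written with δ = 0.183, which is a distinct defect that must be repaired together with this one.

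**What to change.** Use one alpha for the sample size, the Z-test and the confidence limit. Define RD as experimental minus control and compare its upper limit with 0. Then choose one of two options:

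1. **One-sided 0.025.** Keep the 97.5% one-sided limit, run the Z-test at one-sided 0.025, exempt the primary test from the general p < 0.05 threshold, and restate the power in Sample size estimation as about 70% at 92 evaluable per group (about 73% at 97).
2. **One-sided 0.05.** Keep Zα = 1.645, 92 per group and 80% power, replace the limit with a 95% one-sided limit (the upper bound of a two-sided 90% interval), and state openly that the primary claim carries a 5% one-sided error.

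Settle whether enrolment is 208 or 216 at the same time, since the restated power depends on it. The cost is wording and, under option 1, a less favourable stated power. Neither option needs extra patients.
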